### Aims and hypotheses

This RCT aims to assess the following:The feasibility of implementing Cascade nationwide, including the recruitment procedure, response/attrition rates and cost.The efficacy of Cascade in improving the QoL of parents (the primary outcome). Secondary outcomes include parent depression, anxiety, and parenting self-agency, as well as social and emotional functioning of the children in the family.

We hypothesise that delivering Cascade will be feasible and acceptable. We also hypothesise the following:Both the PSG and Cascade participants will show greater improvements in QoL compared with the waitlist control, measured from T1 to T2.Participants who complete Cascade will show greater improvements in their QoL compared to participants who complete the PSG, measured from T1 to T2.

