### Participants

This study will recruit 120 parents (approximately 40 in each arm). This sample size will allow medium-to-large differences in parent QoL to be detected with a power of 80% at a two-tailed significance level of 0.05 (assuming Cohen’s d = 0.65 as the difference in change from time 1 to time 2 for any pair of groups, standardised on the pooled within-group standard deviation). This effect size is clinically significant [38]. It is anticipated that approximately 375 parents will need to be approached to achieve a final sample of 120 participants (assuming a 40% response rate and 20% attrition rate).

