#### Statistical analyses

This trial will employ ‘intention-to-treat’ and ‘as-treated’ analyses. Analyses will be based on mixed random-intercept models that will assess differences between the groups in terms of change in QoL from T1 to T2 (the primary analysis), from T1 to T3, and from T1 to T4. Random intercept models, which utilise maximum-likelihood estimation, provide more efficient estimates of effects with unbalanced data than the traditional repeated measures approach [67]. Multiple regression analyses will be conducted using T1 data to identify demographic and other factors that contribute to treatment outcome. Multiple comparisons will be used to test a priori hypotheses and to conduct post-hoc testing, with the alpha rate adjusted using the Holm-Bonferroni method [68].

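### Plain Holm is valid but needlessly conservative for three pairwise contrasts among three arms; Shaffer's version gains power at no cost in familywise error, and the primary family should be named

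*Protocol article*

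**What the plan says.** The Aims and hypotheses section of the protocol article gives two quality-of-life hypotheses, both on change from T1 to T2. The first is that "Both the PSG and Cascade participants will show greater improvements in QoL compared with the waitlist control", which is two contrasts (peer-support group versus waitlist, Cascade versus waitlist). The second is that Cascade improves more than the peer-support group, which is the third. These are all the pairwise contrasts that three arms allow.

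The Statistical analyses section specifies mixed models for "change in QoL from T1 to T2 (the primary analysis), from T1 to T3, and from T1 to T4". On multiplicity it has one sentence: "Multiple comparisons will be used to test a priori hypotheses and to conduct post-hoc testing, with the alpha rate adjusted", by the Holm-Bonferroni method. It does not say which tests make up a family, or whether the a priori and post-hoc tests are adjusted together or apart.

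The Participants section sizes the trial at about 40 parents per arm "with a power of 80% at a two-tailed significance level of 0.05", taking Cohen's d as "0.65 as the difference in change from time 1 to time 2 for any pair of groups", "standardised on the pooled within-group standard deviation". The section on parent psychosocial functioning names the PedsQL Family Impact Module as the primary psychosocial outcome.

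**The concern.** Holm tests three p-values in order against 0.0167, 0.025 and 0.05. The middle threshold of 0.025 protects against the case where one null is false and the other two are both true. With three arms that case cannot occur: if two of the three pairwise differences are zero, the third is zero as well. The plan therefore pays for protection that it does not need.

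The cost falls on the second-smallest p-value. If it lies between 0.025 and 0.05 after a first rejection, Holm stops and a three-arm procedure would reject. Hypothesis 1 is exposed most, because it needs two rejections. With 40 per arm and sample-size power set at an unadjusted 0.05, there is little slack to give away.

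A second, smaller matter is that the sentence leaves the primary family unnamed. If later tests were counted in the same family as the three primary contrasts, the primary thresholds could be stricter than 0.0167, 0.025 and 0.05.

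**Working it through.** **Inputs.** From the Participants section: 40 per arm, d = 0.65, SD standardised to 1, two-sided 0.05, power 80%, 40% response, 20% attrition. From Aims and hypotheses: three pairwise T1-T2 contrasts. Assumed: independent normal responses and a common variance pooled over the three arms (3 × 40 − 3 = 117 df).

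**1. The plan's own figure.** n per arm = 2(1.960 + 0.842)² / 0.65² = 2 × 7.85 / 0.4225 ≈ 37.2, so 38. At 40 per arm a two-sample t-test has 81.9% power. The approach count is 120 / 0.8 / 0.4 = 375. Both stated figures reproduce, for a single contrast at an unadjusted 0.05.

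**2. Thresholds.** Ordered p-values are compared with:

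- Holm: 0.05/3 = 0.0167, 0.05/2 = 0.025, 0.05.
- Shaffer, three arms: 0.0167, 0.05, 0.05.

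Shaffer's thresholds are never below Holm's, so it never rejects less.

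**3. Error control.** The number of true pairwise nulls can be three, one or none. Two is impossible.

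- Three true: a false rejection needs the smallest p-value to be at most 0.05/3. By Bonferroni the chance is at most 3 × 0.05/3 = 5%.
- One true: a false rejection needs that one p-value to be at most 0.05, so the chance is at most 5%.
- None true: no false rejection is possible.

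Strong control at 5% therefore holds.

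**4. Power by simulation** (200,000 runs; a 400,000-run repeat agreed within 1 percentage point). True means are listed as waitlist, peer support, Cascade.

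| True means | Quantity | Holm | Shaffer | Unadjusted |
|---|---|---|---|---|
| 0, 0, 0.65 | Cascade vs peer support | 72% | 76% | 82% |
| 0, 0.65, 0.65 | both groups vs waitlist | 60-61% | 69% | 72% |
| 0, 0.325, 0.65 | Cascade vs waitlist | 69% | 70% | 82% |
| 0, 0.325, 0.65 | each smaller contrast | 21-22% | 28% | 30% |
| 0, 0.65, 1.3 | Cascade vs peer support | 81% | 82% | 82% |
| 0, 0, 0 | familywise error | 4.3-4.4% | 4.3-4.4% | 12% |
| 0, 0, 0.65 | error on the one true null | 3.3% | 4.9% | 5% |

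An omnibus test at 0.05 followed by pairwise tests at 0.05 is also a closed procedure for three arms. It gives 78% in the first row and 71% in the second.

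**5. If other tests were pooled with the primary three.** Three contrasts at three time points make nine tests, and Holm's first step becomes 0.05/9 = 0.0056. With means 0, 0, 0.65 and six added null tests, power for Cascade versus peer support falls from 72% to about 55% if the added tests are independent, and to 54% if they are correlated at 0.5. If the T2 effect persists at T3 and T4, it is about 59%. These figures apply only under the pooled reading.

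**The case against.** The strongest objection is that nothing here is an error. Holm gives valid strong control of the familywise error, and choosing it over a sharper procedure is a matter of efficiency. That stands. So does the point that the gain varies: about 4 points for Cascade versus peer support when Cascade alone differs, and about 1 point when the arms are well separated.

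A reader might go further and infer that the article places a priori and post-hoc tests in one Holm family, so that every post-hoc test lowers the primary threshold. The document does not support this, for three reasons.

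- The sentence names one method for two uses and does not say that they share a family. Holm within each set is an ordinary reading, and the article separately marks T1-T2 change as the primary analysis and confines both hypotheses to it.
- The T1-T3 and T1-T4 comparisons and the secondary outcomes are planned in the article. They are not chosen after seeing data.
- Even in a pooled family, Holm steps down. An added test that is rejected earlier costs the primary contrasts nothing; only tests not yet rejected lower their threshold.

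A full protocol or analysis plan may also define the families. What remains is that the published sentence leaves this open, and that the step-down rule it does fix can be improved.

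**Conclusion.** This is a free improvement, not a fault in validity. For the three a priori contrasts, Shaffer's modification keeps the familywise error at or below 5%, never rejects less than Holm, and adds about 4 points of power for Cascade versus peer support (72% to 76%) and about 8 to 9 points for hypothesis 1 (60-61% to 69%) in the configurations most relevant to each. The range across the configurations tried is about 1 to 9 points. It recovers part of the power that any multiplicity adjustment costs against the unadjusted calculation, but not all of it.

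The result assumes 40 analysable parents per arm, d = 0.65, independent responses, and three contrasts estimated from the same model in the same analysis set. The last condition matters because hypothesis 2 is worded for participants who complete their programme, and the article plans both intention-to-treat and as-treated analyses. The logical link among the three nulls holds only within one population.

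The pooled-family loss (to about 55% with nine tests) shows why the family should be named. It is not a consequence of the plan as written.

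**What to change.** Replace the multiplicity sentence with wording such as: 'The three pairwise contrasts of T1-T2 change in the PedsQL Family Impact Module, estimated from one model in the intention-to-treat set, form the primary family at two-sided 0.05 and are tested by Shaffer's modification of Holm (0.0167, 0.05, 0.05). Other planned comparisons and post-hoc comparisons are Holm-adjusted in separate families, which do not alter the primary thresholds.'

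The cost is one sentence. No participants, data or models are added, and the method uses the same three p-values that Holm needs. T3, T4 and secondary comparisons keep their Holm adjustment, so they need not be demoted to unadjusted exploratory tests. The one consequence to accept is that the 5% error rate then applies within each family and not across all families together. The article does not claim the latter. The change should be made before outcome data by arm are seen.

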## Discussion

This paper outlines the protocol for a multisite trial of a novel online intervention for parents of children who have recently completed treatment for cancer, entitled Cascade. The Cascade program is unique because (i) it targets parents *and* assesses the possible impact of the intervention on children in the family and (ii) its online delivery reduces geographical and physical isolation. The planned RCT is methodologically rigorous since it follows gold-standard guidelines, includes both an active and waitlist control, and employs strict treatment fidelity assessments.

The technology used to deliver Cascade is an important innovation, as it enables the provision of evidence-based support to families dispersed across metropolitan, rural and remote regions. Cascade is part of a broader telehealth movement bringing about change in the way that mental health care is delivered worldwide, in response to factors such as geographical isolation and limitations of time and resources [69-72]. There is growing evidence supporting the potential of telepsychology in treating disorders such as anxiety and depression [31,73,74]. Evidence suggests that core aspects of CBT such as cognitive challenging, role-playing and modelling, setting up behavioural experiments and homework assignments, translate well over videoconferencing [75]. Further, videoconferencing does not appear to diminish facilitator competence, adherence, or patient perceptions of rapport or empathy conveyed by the facilitator [74]. However, as most ‘online therapies’ are self-guided by the user with telephone/email-based support [76], few manualised treatment programs or best-practice guidelines exist to guide Cascade in aspects relating to therapy process and online interaction. This may mean that facilitator practice effects occur across the study period, as the facilitator gains competency in anticipating, and managing, challenges in the videoconferencing environment.

Despite its strengths, the Cascade study design also has methodological vulnerabilities. The three-armed design will increase the time it takes to recruit sufficient participant numbers. In addition, the 6-month follow-up is another aspect of the study design that, although methodologically important, may add complexities to final data analyses. Participants may differ in terms of psychosocial support services they receive in this time, and the number of other parents of childhood cancer survivors they come into contact with. Individual differences in additional support services and peer support is likely to be important throughout the trial. These factors will require careful monitoring and documentation, and will need to be taken into account in data analyses/interpretation.

In sum, Cascade is a selective preventative program with the potential to avoid mental health problems in parents and other family members by equipping parents with coping skills to manage the challenges of the survivorship period. This study trials a new model of healthcare delivery that can extend the reach of support to isolated populations worldwide. If this study demonstrates significant improvements in QoL, Cascade will be made available for use with the parents of childhood cancer survivors across Australia, with the potential to be delivered internationally as well.

## Trial status

This is a clinical trial with ongoing patient recruitment. Recruitment for this project commenced in September 2014 and is expected to be completed by June 2016. This trial is recorded under the number ACTRN12613000270718.

## Abbreviations

CBT: cognitive-behavioural therapy
ETT: Emotion Thermometers Tool
PAIS: Psychosocial Adjustment to Illness Scale
PROMIS: Patient-reported Outcomes Measurement Information System
PSG: peer support group
QoL: quality of life
RCT: randomised controlled trial
SPSS: Statistical Package for the Social Sciences
